### 2.5. Sample Size and Power

Sample size is justified a priori following current recommendations [70], with all calculations derived analytically from noncentral *F*, t, and chi-square distributions at a two-tailed significance threshold of α = 0.05 and a target power of 1 − β = 0.80, reproducible in G*Power 3.1 (“ANOVA: Repeated measures, within factors”) and consistent with recent tutorials on power analysis for repeated-measures designs [63]. The primary test is a repeated-measures ANOVA (four within-subject levels) on each composite score. Assuming a correlation between repeated measurements of ρ = 0.50 (a typical value for repeated attitudinal ratings, to be verified in the pilot), the minimum sample is 24 participants for medium effects (*f* = 0.25) and 138 for small effects (*f* = 0.10); under the conservative assumption ρ = 0.30, these become 32 and 193, respectively. The minimum analyzable threshold is therefore set at *N* = 140 valid participants, sufficient to detect even small between-scenario effects under realistic conditions. Because these thresholds depend on ρ, an adaptive rule is pre-registered for the case in which the pilot estimate falls outside the assumed ρ = 0.30–0.50 range. The pilot returns $\hat{\rho }$ with a 95% confidence interval, and every threshold is recomputed at its lower bound, ρ_L_, which is the conservative choice. The number of valid participants required to detect *f* = 0.10 at power 0.80 is 274, 247, 220, 193, 165, and 138 for ρ_L_ = 0, 0.10, 0.20, 0.30, 0.40, and 0.50, respectively; an intermediate ρ_L_ is rounded down to the nearest tabulated value, so that the rule is fully determined in advance for any estimate the pilot can return. Two consequences follow. The recruitment target does not change because the requirement is a decreasing function of ρ and reaches only 274 in the theoretical worst case of ρ_L_ = 0; *N* = 300 preserves power ≥0.80 against small between-scenario effects for every value ρ can take, and the target is in any case set by the person-level analyses described below, which do not depend on ρ. The analytic floor does change: it is redefined as the value tabulated above for the observed ρ_L_, so that it remains at the pre-specified *N* = 140—rounded up from 138—only when ρ_L_ ≥ 0.50 and rises to 165, 193, 220, 247, or 274 as ρ_L_ falls to 0.40, 0.30, 0.20, 0.10, or 0. A ρ_L_ below 0.10 would in addition indicate that the composites are unstable across repetitions rather than that participants are inconsistent, and would therefore also trigger re-inspection of pilot reliability and of the measurement-invariance assumptions before the main study is launched. Any application of this rule, and the $\hat{\rho }$ that triggered it, will be recorded in the pre-registration and reported in the results article.

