
The recruitment target is *N* = 300 valid participants. This target is dictated not by the within-subjects effects (for which power at *N* = 300 is 0.99 for small effects at ρ = 0.50, with a minimum detectable effect of *f* = 0.07), but by the person-level analyses: the familiarity moderation (minimum detectable interaction *f*^2^ = 0.037 at *N* = 300), the global preference test (minimum detectable *w* = 0.21 on 5 degrees of freedom), and descriptive analyses of demographic subgroups. A small interaction effect (*f*^2^ = 0.02) would require *N* ≈ 550; H4 therefore remains partially exploratory, and a non-significant result will not be interpreted as evidence of absence. At *N* = 300, dependent pairwise comparisons detect differences from *dz* = 0.16 (uncorrected) and *dz* = 0.20 (at the Bonferroni bound for six pairwise comparisons), so all six scenario contrasts can be treated as confirmatory. Counterbalancing entails no loss of sensitivity for the primary comparisons: with sequence entered as a four-level between-subjects factor, the autonomy main effect retains 3 degrees of freedom and the same noncentrality, so the minimum detectable effect at *N* = 300 remains *f* = 0.07. The scenario × sequence interaction—the direct test of order dependence—carries 9 degrees of freedom and a minimum detectable effect of *f* = 0.08 at ρ = 0.50 (*f* = 0.10 at ρ = 0.30), giving power of 0.95 against a small order effect of *f* = 0.10; the serial-position main effect in the additive model carries 3 degrees of freedom and matches the sensitivity of the autonomy effect itself. Order artifacts large enough to masquerade as the hypothesized autonomy gradient are therefore detectable, rather than being assumed away. In the pilot, by contrast, the ascending and descending arms (*n* = 25 each) bound order effects only at *f* = 0.17, which excludes medium-to-large artifacts but not small ones; the definitive test is the main-study interaction. Table 2 summarizes the power analysis, and Figure 1 shows achieved power as a function of the number of valid responses.

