The per-scenario response block contains nine Likert items measuring the three primary dependent variables—acceptability (ACC1–ACC3), trust (TRU1–TRU3), and perceived risk (RSK1–RSK3)—followed by six responsibility items (RES1–RES4: surgeon, hospital, AI developer, unavoidable medical uncertainty; RES5: the surgeon’s moral duty to verify AI outputs; RES6: outcome-independent accountability), two manipulation-check items (MAN1: perceived AI control over the final surgical decision; MAN2: perceived technical sophistication of the system), and a perceived difficulty item (DIF1). All scaled items use 7-point end-anchored Likert response formats. Composite scores are computed as the arithmetic mean of their items after reverse-scoring RSK1 (8 − score), which is the only reverse-keyed item in the response block; higher risk scores indicate higher perceived risk. Treating item means on end-anchored 7-point scales as quasi-continuous interval variables is standard practice in experimental vignette research; ordinal-model sensitivity analyses are nevertheless planned in line with current guidance on Likert-based outcomes [62,71]. Table 4 summarizes the measurement structure; per-scenario variables carry the scenario suffix (e.g., ACC1_A, ACC1_B, ACC1_C, ACC1_D).

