
### 2.9. Statistical Analysis

#### 2.9.1. Primary Analyses

Each composite score (acceptability, trust, perceived risk) will be analyzed by a mixed repeated-measures ANOVA, with autonomy level (four scenarios) as the within-subjects factor and presentation sequence (four Williams sequences) as the between-subjects factor. The Greenhouse–Geisser correction will be applied when Mauchly’s test indicates a sphericity violation (Huynh–Feldt for ε between 0.75 and 1), and the multivariate approach (Pillai’s criterion) will be reported in parallel as a sphericity-robust check. H1 and H2 will be tested with within-subjects trend contrasts across the autonomy gradient. Because acceptance need not fall in a straight line, the complete set of orthogonal polynomial contrasts—linear, quadratic, and cubic—is pre-specified, and each is reported together with the proportion of the omnibus effect it accounts for. A purely linear profile leaves the quadratic and cubic components negligible, whereas a step between two adjacent levels appears as a large linear component accompanied by a substantial quadratic or cubic one. Because every monotone step is linear-dominant, the polynomial decomposition establishes departure from a straight line but cannot by itself locate the break; the break is identified only from the Holm-corrected adjacent-pair contrasts (A–B, B–C, C–D). A quadratic-dominant profile with a small linear component would instead indicate a non-monotone pattern, which the hypotheses do not predict and which would be reported as such. A non-monotonic or threshold pattern will be reported as such rather than summarized by the linear trend alone. Post hoc comparisons use dependent-samples *t*-tests for the six scenario pairs with Holm’s sequential correction, applied within each hypothesis-defined family of tests in line with current guidance on multiplicity control [74]. Effect sizes will be reported as partial η^2^ for omnibus tests and Cohen’s dz for pairwise comparisons, with 95% confidence intervals, following effect-size-centered reporting recommendations [64]. Assumption checks include graphical inspection of difference-score distributions; as a distributional robustness analysis, the Friedman test with Holm-corrected Wilcoxon signed-rank pairwise comparisons will be reported alongside each primary test—supplemented by ordinal (cumulative-link) models as sensitivity analyses for the Likert-based outcomes [71]—and the concordance of parametric and nonparametric conclusions stated explicitly. Order dependence is tested directly as the scenario × sequence interaction; a non-significant interaction, together with equivalence of the four sequence-specific profiles, supports pooling across sequences. Independently of that test, the autonomy effect is re-estimated from a linear mixed model with random intercepts per participant and additive fixed effects of autonomy level and serial position (1–4). The Williams square renders this model identified, so the estimate is adjusted for arbitrary—not merely linear—serial-position and fatigue effects, while first-order carry-over is balanced by the design rather than modeled; position-adjusted and unadjusted estimates are reported side by side, and any material divergence between them is treated as evidence of an order artifact and interpreted accordingly. Perceived difficulty (DIF1) and perceived technical sophistication (MAN2) are each added as time-varying covariates in further sensitivity models, addressing fatigue and the possibility that responses track the apparent complexity of the system rather than its autonomy. Finally, between-person heterogeneity in response profiles is examined by adding a random slope for the linear autonomy contrast and testing the improvement in fit by a likelihood-ratio test; a substantial random-slope variance indicates that an average trajectory conceals distinct response patterns and licenses the exploratory typology described in Section 2.9.2. Because a non-significant test is not evidence of absence, a smallest effect size of interest of *dz* = 0.20—the value detectable at the Bonferroni bound for the six pairwise contrasts at *N* = 300—is fixed in advance, and equivalence testing by two one-sided tests against that bound is reported alongside every null pairwise result, so that any claim that two adjacent scenarios do not differ rests on an equivalence test rather than on the absence of significance.

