
#### 2.9.2. Secondary and Exploratory Analyses

(i) Moderation (H4): the scenario × AI familiarity (B1, centered) interaction, via repeated-measures ANCOVA or a linear mixed model with random intercepts per participant, the recommended framework for vignette data [62]; presentation sequence is retained as a between-subjects factor here, as in every repeated-measures model in this protocol. (ii) Person-level multiple regression: mean acceptability across scenarios predicted by AI familiarity, general AI attitudes, and demographics (reporting *B*, *SE*, β, 95% CI, R^2^, VIF). (iii) Responsibility migration (H3): a 4 × 4 mixed ANOVA (scenario × actor, RES1–RES4, both within-subjects; presentation sequence between-subjects) with Greenhouse–Geisser correction; the scenario × actor interaction is the direct test of H3. Because H3 is confirmatory, it receives the same order controls as H1 and H2: the sequence terms are inspected first, and the migration estimate is repeated in a linear mixed model containing an additive serial-position term. (iv) Responsibility concentration: a normalized Herfindahl–Hirschman index computed per scenario from the relative weights of the three responsible actors (surgeon, hospital, AI developer; RES4—unavoidable medical uncertainty—is not a responsible actor and is analyzed separately), compared across scenarios by mixed repeated-measures ANOVA with sequence as a between-subjects factor; low values index diffusion of responsibility across actors, operationalizing the “problem of many hands” described in the responsibility literature [44,45]. (v) RES5 (moral duty) and RES6 (outcome-independent accountability): mixed repeated-measures ANOVAs across scenarios with sequence as a between-subjects factor, Holm-corrected within the family. (vi) Global preference (P1): a goodness-of-fit chi-square with standardized residuals over six analysis categories on 5 degrees of freedom. The six categories are the four scenarios, “I would prefer AI not to be involved in any way,” and a combined “no clear preference” category; the last pools the item’s two undecided options (“I have no preference” and “I cannot decide”), which are combined a priori because neither expresses a preference between scenarios and each is expected to be sparse. Consistency between stated preference and each participant’s maximum-acceptability scenario is reported descriptively. (vii) Exploratory: P4a and P4b (the surgeon’s permanent legal and, separately, moral responsibility) analyzed descriptively, compared with each other by a dependent-samples test on the within-person difference, and correlated with RES5/RES6; free-text concerns (P2) summarized by brief thematic analysis. (viii) Sensitivity analyses: primary analyses repeated (a) excluding participants with a single attention-check failure (who are retained under the primary rule) and (b) excluding participants with any comprehension failure, to demonstrate that conclusions do not depend on the cleaning criteria [69]. (ix) Order effects: descriptive profiles by sequence, the scenario × sequence interaction with its effect size and 95% confidence interval, and sequence-specific manipulation-check profiles. (x) Response-pattern typology (exploratory): where the random-slope test of Section 2.9.1 indicates heterogeneity, individual acceptability trajectories across autonomy levels are classified by latent-class growth analysis, with class enumeration by BIC and entropy and a minimum class size of 5% fixed in advance, and class membership described against AI familiarity, healthcare-system trust, and demographics; no inferential claim is attached to this analysis. (xi) Healthcare-system trust (B6) enters the person-level regression of (ii) as a covariate and is examined as an exploratory moderator of the autonomy effect, alongside healthcare contact frequency (B5) and prior surgical experience (B4, B4a). (xii) Subgroup analyses, all of which are secondary or exploratory, are governed by a minimum-cell rule fixed in advance: inferential tests within a subgroup are reported only where that subgroup contains at least 50 valid participants, the size at which a within-subject difference in *dz* = 0.40 is detectable at power 0.80; subgroups of 30–49 are reported descriptively with 95% confidence intervals and labeled as underpowered; subgroups below 30 are pooled into a residual category or not reported. A difference between subgroups is never inferred from a significant effect in one and a non-significant effect in another; only the formal interaction term, with its own confidence interval, supports such a claim. The set of moderators is fixed a priori, in the pre-registration, to seven: AI familiarity (B1), healthcare-system trust (B6), healthcare contact frequency (B5), prior surgical experience (B4/B4a), education (D3), age (D2), and field of activity (D4). Results are reported for all seven irrespective of significance, and no further moderator is added after the data are seen. (xiii) Missing data: because all closed items are mandatory, missingness in the dependent variables is structurally impossible within a submitted questionnaire. Two other forms of missingness remain. The first is unit-level, from questionnaires abandoned before submission. The platform is configured not to store partial submissions, so responses from abandoned questionnaires are neither retained nor analyzed (Section 2.10 and Appendix A.1). Attrition is therefore characterized from the platform’s page-level counters—how many participants reached each page—rather than from partial response data, and is reported as drop-out by serial position in the participant-flow diagram. Analyses are accordingly restricted to complete cases, that is, participants with all four scenario blocks, and no imputation is performed: with no partial records retained, there are no incomplete cases to impute. The second is item-level, on the background and demographic items that offer a “prefer not to answer” option or, in the case of B4 and B4a, are not displayed where the explicit health-data consent is declined; these are treated as a distinct category descriptively and as missing in inferential models, with a sensitivity analysis retaining the category in the person-level regression. Because complete-case analysis is not neutral when attrition is differential, drop-out is compared across the four presentation sequences, and any imbalance is reported and carried into the interpretation of the order analyses. All tests are two-tailed at α = 0.05, with exact *p*-values, effect sizes, and 95% confidence intervals reported for all tests, including non-significant ones. On closed 1–7 scales, no distribution-based outlier removal is applied.

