Scenario × sequence interaction—order test (*df* = 9)	*N* = 300, ρ = 0.50	*f* = 0.08
Scenario × sequence interaction—order test (*df* = 9)	*N* = 300, ρ = 0.30	*f* = 0.10
Pilot order bound, ascending vs. descending arm (*df* = 3)	*N* = 50, ρ = 0.50	*f* = 0.17
Dependent comparison within a demographic subgroup	*n* = 50, α = 0.05	*dz* = 0.40

Abbreviations: RM-ANOVA, repeated-measures analysis of variance; *N*, number of valid participants; *n*, number of participants per pilot arm or subgroup; ρ, correlation between repeated measurements; α, significance threshold; *df*, degrees of freedom; f and *f*^2^, Cohen’s effect-size indices for *F* tests; *dz*, Cohen’s effect size for dependent-samples comparisons; *w*, effect size for the goodness-of-fit chi-square test.

**Table 3 healthcare-14-03030-t003:** Projected recruitment funnel.

Stage	Assumed Pass Rate	Estimated Number
Link accesses	—	≈545
Begin questionnaire (consent given)	85% of accesses	≈463
Eligible after screening (items S1, S2)	96% of starters	≈445
Completed (submitted) questionnaires	75% of eligible	≈334
Valid after quality exclusions (ATT, CC, invariant, duplicates)	90% of submitted	≈300

Abbreviations: S1 and S2, the two screening items of the instrument (Appendix A.1); ATT1 and ATT2, attention checks; CC_A–CC_D, comprehension checks.

**Table 4 healthcare-14-03030-t004:** Measurement structure of the instrument.

Construct/Variable	Items	Scale	Role in Analysis
Acceptability	ACC1–ACC3 (mean), per scenario (×4)	Likert 1–7	Primary DV (H1), within-subjects
Trust	TRU1–TRU3 (mean), per scenario (×4)	Likert 1–7	Primary DV (H1), within-subjects
Perceived risk	RSK1 (reversed), RSK2, RSK3 (mean), per scenario (×4)	Likert 1–7	Primary DV (H2), within-subjects
Responsibility attribution	RES1–RES4, per scenario (×4)	Likert 1–7	Secondary DV (H3), within-subjects
Responsibility principles	RES5, RES6, per scenario (×4)	Likert 1–7	Secondary DV
Global preference	P1	7 response options (6 analysis categories)	Secondary DV
General acceptability	P3	Likert 1–7	Secondary DV
AI familiarity	B1	Likert 1–7	Moderator (H4)/covariate
General AI attitudes	G1–G4 (G2, G4 reversed)	Likert 1–7	Covariates
Experience and demographics	B2–B5, D1–D7	Mixed	Covariates/sample description
Manipulation check (perceived AI control)	MAN1, per scenario (×4)	Likert 1–7	Design validation
Scenario difficulty	DIF1, per scenario (×4)	Likert 1–7	Control covariate (fatigue)
Data quality	ATT1, ATT2, CC_A–CC_D	Categorical	Exclusion criteria

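### H3 is confirmatory and directional, but its named test is a raw-scale scenario × actor interaction on single 7-point items, which can be significant without any surgeon-to-developer shift

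*Protocol article*

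**What the plan says.** Section 1.6 words H3 as a directional statement about two parties, surgeon and developer. It adds that H1–H3 are each tested by an omnibus autonomy effect followed by polynomial contrasts. Section 2.12 lists H3 among the confirmatory hypotheses, while Table 4 gives RES1–RES4 the role "Secondary DV (H3), within-subjects".

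Section 2.9.2(iii) and Table 5 specify a 4 × 4 ANOVA (scenario by actor, with sequence between subjects) and name the scenario × actor interaction as the direct test. For H3, Table 5 lists F, degrees of freedom, p, partial η² and ε. It lists no surgeon or developer trend and no direction. The added controls are introduced with "Because H3 is confirmatory, it receives the same order controls as H1 and H2".

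The other safeguards are worded as follows:
- **Interval scale (2.6):** "Treating item means on end-anchored 7-point scales as quasi-continuous interval variables is standard practice in experimental vignette research". The same sentence goes on to announce ordinal-model sensitivity analyses for Likert-based outcomes.
- **Distribution (2.9.1):** the Friedman and Wilcoxon tests "will be reported alongside each primary test—supplemented by ordinal (cumulative-link) models as sensitivity analyses for the Likert-based outcomes".
- **Cleaning rules (2.9.2(viii)):** the primary analyses are repeated under two stricter exclusions.

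Section 2.6 has participants rate each party separately, not as shares of a fixed total. Section 3 expects the surgeon to carry the dominant share at low autonomy.

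**The concern.** The plan accepts that confirmatory status earns H3 extra protection, but spells this out only for order effects. What remains is an undirected 9-df interaction on bounded single items, serving as the decision rule for a directional claim about two of the four items.

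Two things can go wrong. First, any departure from parallel profiles counts, including one confined to the hospital or to unavoidable uncertainty. Second, ratings are not shares, so all four can rise together. If the surgeon starts near 7, that item is compressed, and equal underlying rises give unequal raw slopes. A raw developer-minus-surgeon contrast is distorted in the same way. The within-person account of responsibility migration, which the Discussion presents as a main contribution, could then rest on the end of the response scale.

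**Working it through.** **1. The plan's own figures.** Section 2.5 states "The primary test is a repeated-measures ANOVA (four within-subject levels) on each composite score". With λ = N·m·f²/(1 − ρ), m = 4, df₁ = 3 and df₂ = 3(N − 1), taking N = 138, f = 0.10 and ρ = 0.50 gives λ = 138 × 4 × 0.01/0.50 = 11.04 and power 0.80. The stated 138 is reproduced. At N = 300, power is 0.99 (ρ = 0.50) and 0.95 (ρ = 0.30), also as stated. None of these figures concerns the scenario × actor test.

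**2. The ceiling mechanism.** Let a rating be a normal latent score (mean μ, SD σ), rounded and clipped to 1–7. Its expected value is E = 1 + Σₖ₌₁…₆ [1 − Φ((k + 0.5 − μ)/σ)]. For μ = 6.0 and σ = 1.4 the six terms are 0.999, 0.994, 0.963, 0.858, 0.640 and 0.360, so E = 5.81. Give every party the same latent rise of 0.25 per step, that is 3 × 0.25 = 0.75 from A to D:

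| Item | Latent mean in A | Observed A → D | Observed rise |
|---|---|---|---|
| Developer | 4.0 | 4.00 → 4.72 | 0.72 |
| Surgeon | 5.5 | 5.41 → 6.00 | 0.59 |
| Surgeon | 6.0 | 5.81 → 6.32 | 0.51 |
| Surgeon | 6.6 | 6.23 → 6.61 | 0.38 |

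No responsibility has moved, yet the developer's raw rise exceeds the surgeon's by 0.13, 0.21 and 0.34 points.

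**3. Rejection rates, N = 300, equal latent rise, no transfer.** The inputs are assumptions: latent SD 1.4; variance shares 0.4 person, 0.2 person × actor, 0.4 residual. The interaction is tested by a 9-df multivariate test and the contrast by a t-test on the linear developer-minus-surgeon trend.

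| Surgeon's observed mean in A | Interaction, 0.25 per step | Raw contrast, 0.25 per step | Interaction, 0.10 per step |
|---|---|---|---|
| 5.4 | 15% | 28% | 5% |
| 5.8 | 55% | 64% | 7% |
| 6.2 | 97% | 97% | 17% |

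Repeat runs give 48% to 55% for the interaction in the middle row, and up to 21% in the last cell. With no rise, the rates stay at about 5%.

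**4. The planned ANOVA under other assumptions.** This run uses sequence between subjects, the Greenhouse–Geisser correction, latent SD 1.5, shares 0.3/0.2/0.5 and a developer latent mean of 3.5. Interaction rejection rates by **total** A → D rise:

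| Surgeon latent mean | 0.25 | 0.5 | 1.0 |
|---|---|---|---|
| 5.5 | 6% | 6% | 27% |
| 6.0 | 5% | 14% | 67% |
| 6.5 | 9% | 25% | 98% |

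At N = 140 the last row becomes 5%, 12% and 58%. With no truncation, or with all four items mid-scale, the rate is about 5%, so the excess comes from the ceiling.

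**5. Undirectedness without any ceiling.** At N = 300 with all items mid-scale, the interaction rejects in 97% of studies if only RES4 falls by 0.5, in 96% if only the hospital rises by 0.5, and in 100% if the shift runs from developer to surgeon.

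**6. What separates the two explanations.** A rule that needs a significantly falling surgeon trend and a significantly rising developer trend fires in 0% of the equal-rise runs. In the 0.25-per-step runs the surgeon's trend is significantly positive in 100% of studies. A clustered ordered probit rejects in 5–6% when latent SDs are equal across actors, but in 23–35% when they differ (surgeon/developer 1.2/1.6, 1.1/1.7 or 1.7/1.1).

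**The case against.** A reader might infer that H3 receives no distributional check at all. The documents do not support that. The interval-scale sentence in 2.6 itself announces ordinal models for Likert-based outcomes, 2.9.1 uses the same phrase, and Table 4 lists RES1–RES4 as Likert 1–7. The ordinal models may well be meant to reach them. What stands is that the wording leaves this open.

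A reader might also infer that the artifact would pass unseen. It need not: the surgeon's rating rises in every such run, so scenario means by actor would show it, and a careful analyst would not call that migration. Section 1.6 also promises polynomial contrasts for H3. But these are not carried into 2.9.2(iii) or Table 5, where significance of the interaction is the stated criterion.

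The rates rest on assumed means, SDs and rises. A dominant share need not lie near the scale end, and an equal rise for all four loci is not what the plan expects. That objection stands and limits the claim to what can happen. So does the objection that making the ordinal model a compulsory gate would swap one scale assumption for another, as step 6 shows.

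**Conclusion.** The point holds in conditional form. The named H3 test does not test H3's direction, and it cannot distinguish a ceiling-compressed general rise from a transfer. The undirectedness follows from the text and needs no assumption about means. The size of the ceiling effect does: at N = 300 it runs from negligible (about 5–9% rejection for a total rise of 0.25 to 0.30 points with the surgeon's observed mean in A at 5.8 or below) to near certain (97–98% for a total rise of 0.75 to 1.0 with that mean at about 6.1–6.2). The documents give no responsibility means or SDs to place the study within that range, so they do not support saying that a false migration finding will be reported. The incomplete robustness coverage is secondary: the rank-based and cleaning analyses are written for primary analyses, and the ordinal coverage is ambiguous. This should be settled before pre-registration.

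**What to change.** In 2.9.2(iii) and Table 5:

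1. Pre-specify the autonomy trends for RES1 (surgeon) and RES3 (developer), with estimates and confidence intervals. Call H3 supported only if the surgeon's rating falls and the developer's rises. Keep the scenario × actor interaction as the omnibus result.
2. State that the cumulative-link sensitivity model covers RES1 and RES3, with an actor × autonomy trend and participant-level clustering. Report its concordance with the ANOVA as a sensitivity result, not as a sole gate.
3. Extend sensitivity analyses (viii)(a) and (b) to H3.

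The cost is some wording, a little more analysis and one more model of a type already planned. No new items or participants are needed, and no data have been collected. H3 becomes somewhat harder to claim: a developer rating that rises while the surgeon's stays flat would no longer count as support, which matches H3 as worded.
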